    1. ACEI
    2. ARBs
14. Medications during Hospitalization
    1. ACEI
    2. ARBs
    3. Azithromycin
    4. Remdesivir
    5. Steroids
    6. Chloroquine
    7. Hydroxycloroquine
15. Highest level of respiratory support prior to convalescent plasma transfusion
    1. Non-invasive positive pressure
    2. Mechanical ventilation
    3. ECMO

**Statistical Analysis Plan (version 5.0)**

**Date:** 27 July 2020

## Statistical Hypotheses

**Primary Hypothesis:** 7-Day and 30-Day mortality will be affected by plasma transfusion dynamics after adjustment for pre-disposing risk factors. Transfusion dynamics are defined in the context of timeliness of transfusion relative to date of diagnosis, the volume of plasma initially given (i.e., on the first transfusion day), and the quantity of neutralizing antibodies on the first day of transfusion.

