4.3 JUSTIFICATION FOR DOSE

Initial data available from studies using COVID-19 convalescent plasma for the treatment of individuals with severe or life-threatening disease indicate that a single dose of 200 mL showed potential efficacy. The volume of plasma to be transfused should be based upon the patient’s weight and clinical comorbidities (e.g. patients with impaired cardiac function and heart failure may require less volume or more prolonged transfusion times). The volume of plasma to be transfused should be at least one unit (approximately 200 mL) but may be greater if the treating clinician concludes a larger volume is appropriate. Transfusions may occur at any time throughout the hospitalization including multiple doses on non-sequential days. In general, it is expected that most patients will receive two units or less, but this language is not intended to restrict the use of convalescent plasma in larger quantities when the treating physician determines that such volumes and/or re-treatment are clinically justified.

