**Risk Modifiers**

1. COVID-19 Severity
2. At risk of severe / life threatening COVID-19
3. Currently has severe / life threatening COVID-19 with further delineation of why (Y/N to each of the following: dyspnea, respiratory rate >=30/min, spo2 <= 93%, p/f <300, lung infiltrates > 50 within 24 – 48 hrs, respiratory failure, septic shock, multi-organ dysfunction or failure)
4. Body Composition: Height, Weight, BMI
5. Race
6. Ethnicity
7. Gender/Sex
8. No. of days from Covid-19 symptom onset to convalescent plasma transfusion
9. No. of hospitalized days prior to convalescent plasma transfusion
10. No. of days in the ICU prior to convalescent plasma transfusion
11. No. of days receiving mechanical ventilation prior to convalescent plasma transfusion
12. Pre-existing conditions
    1. Lung disease
    2. Cardiovascular conditions
    3. Obesity

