## Primary Analysis Plan

### Preparation of the survival endpoint: The timing of death is recorded only with the precision of a calendar day, so adjustments are needed to develop the survival estimates. For deaths that occur on the same day of transfusion, a death indicator representing 0.5 days will be administratively assigned. Otherwise, the number of days between the date of the first transfusion and death will be calculated for each participant. For patients transfused without a death record recorded as an SAE, or more precisely, on the death case report form, they are assumed to be alive. Within the context of the report and programming, this is denoted as the "immortal" survival assumption. To minimize extrapolation of the survival curves beyond a reasonable time that this assumption could be upheld, survival estimates are limited to 30 days; however, the report does introduce stopping the survival curves early, for example, at Day 7 for 7-Day mortality estimates.

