### Primary Data Analysis: The primary analysis will be conducted through a series of unadjusted and adjusted survival models. This is required given the study is non-randomized and factors that may affect overall survival may serve as a confounding variable in the analysis. The primary hypothesis presents three variables that are hypothesized to have an impact on mortality.

First, the time to transfusion is considered. Based on early reports with convalescent plasma, a target window of 0 days, 1-3 days was considered optimal. Therefore, patients are divided into a group representing "timely" delivery of convalescent plasma. The remaining subjects are split into two groups, Days 4-10 (i.e., a week following a timely period) and Days 11+. In some analyses to aide in the graphical presentation of the data, the timeliness data is dichotomized into <=3 days vs. 4+ days.

Second, the transfusion volume on the first day of transfusion (if more than 1 transfusion was given). For this analysis, various categorizations of the volumes were considered, however, for the primary analysis, a spilt at 225 ml was implemented. This effectively separates people that received 1 unit (~ 200ml) from those that deliberately received more than 1 unit of plasma. 225 ml was selected to all for some variance in the volume in the first unit of plasma.

For the final component of the analysis, the neutralizing antibodies are both semi-quantitative and categorical in interpretation. There are lab established thresholds for negative (<1:80) and serial dilution allows for estimates ranging from 1:80 to >=1:2560. The analysis will consider the levels of the titers as nominal values as well as introducing some thresholds to classify the titers into a "low" vs. "high" classification. The original statistical analysis plan consisted of a planned analysis of the titer data using a splined fit on the observed antibody concentration. The spline was to avoid a strong linear assumption on the relationship of the titer and survival. The decision to use that approach was changed post hoc to the dichotomized approaches to account for the lack of dose-response relationship observed with the data. This decision allowed for simplification of the data presentation.

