6. BMI
7. ICU at time of Covid-19 convalescent plasma transfusion
8. Level of respiratory support at time of Covid-19 convalescent plasma transfusion
9. Body Composition: Height, Weight, BMI
10. No. of days from Covid-19 symptom onset to convalescent plasma transfusion
11. COVID-19 Severity
12. At risk of severe / life threatening COVID-19
13. Currently has severe / life threatening COVID-19 with further delineation of why (Y/N to each of the following: dyspnea, respiratory rate >=30/min, spo2 <= 93%, p/f <300, lung infiltrates > 50 within 24 – 48 hrs, respiratory failure, septic shock, multi-organ dysfunction or failure)

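### SAP v5.0 names no pre-existing condition to adjust the first-day volume comparison, although the protocol bases volume on comorbidity, and it lets same-day deaths help decide the volume group

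*Supplement*

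**What the plan says.** **How volume is chosen.** Protocol v10.0 section 4.3 bases volume on the patient's weight and clinical comorbidities. Its example is that "patients with impaired cardiac function and heart failure may require less volume or more prolonged transfusion times". The floor is about one unit, "but may be greater if the treating clinician concludes a larger volume is appropriate". Section 6.1.2 leaves the timing of any subsequent unit to the treating physician, according to the patient's condition.

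**How volume is analysed.** SAP v5.0 (Statistical Hypotheses) states that "7-Day and 30-Day mortality will be affected by plasma transfusion dynamics after adjustment for pre-disposing risk factors". Volume on the first transfusion day is one of three exposures, and "for the primary analysis, a spilt at 225 ml was implemented". The SAP describes the upper group as patients who were deliberately given more than one unit.

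**What is adjusted for.** SAP v5.0 recognises that the study is non-randomized and open to confounding. It describes the Cox covariates only as a set to be controlled for and does not list them. Its one list of variables, Risk Modifiers, is introduced for future secondary strata. It holds calendar month, demographics, body size, ICU status, "Level of respiratory support at time of Covid-19 convalescent plasma transfusion", days from symptom onset and acute severity items. It holds no pre-existing condition. The Risk Modifiers list of SAP v2.0 did, including "Cardiovascular conditions", lung disease, diabetes and immunosuppressive therapy.

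**Time origin.** Survival runs from the date of the first transfusion. "For deaths that occur on the same day of transfusion, a death indicator representing 0.5 days will be administratively assigned"

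**The concern.** A comorbidity that influences both the volume given and the risk of death is a confounder of the volume comparison. The protocol itself says that comorbidity influences volume. The SAP's promise to adjust for pre-disposing factors cannot be checked for the factor that matters most here, because no such factor is named.

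The second problem is one of timing, and baseline adjustment does not remove it. Exposure is the total given over the first day, but follow-up starts at the first transfusion. A patient who dies that day before a further unit can be started is classed as low volume because of the death.

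At stake is a primary contrast. SAP v5.0 directs anyone wanting inference to the hazard ratio and its test, so a modest bias in a large cohort could be taken for a volume effect.

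**Working it through.** The documents give no effect size, power figure, mortality rate or volume distribution for this comparison, so there is no planned figure to reproduce. The calculations below size each path on its own with no true volume effect. Except where marked, the inputs are assumptions.

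**1. Confounding by cardiac impairment**

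Inputs:
- P(>225 mL) without cardiac impairment: 0.5
- prevalence of cardiac impairment, *c*: 10% to 30%
- odds ratio for receiving >225 mL with cardiac impairment, *OR*: 0.33 to 0.8
- mortality ratio for cardiac impairment, *R*: 1.25 to 2.0

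Formulas:
- P(>225 mL with impairment) = *OR*/(1 + *OR*), because the reference odds are 1
- prevalence of impairment in each volume group, p_high and p_low, by Bayes' rule
- apparent RR (high vs low) = [1 + p_high(R − 1)] / [1 + p_low(R − 1)]

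| Case | c | OR | R | p_low | p_high | Apparent RR |
|---|---|---|---|---|---|---|
| Weakest | 0.10 | 0.80 | 1.25 | 0.110 | 0.090 | 1.0225/1.0275 = 0.995 |
| Middle | 0.20 | 0.50 | 1.50 | 0.250 | 0.143 | 1.0714/1.1250 = 0.952 |
| Strongest | 0.30 | 0.33 | 2.00 | 0.392 | 0.175 | 1.1754/1.3919 = 0.844 |

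For the middle case, P(>225 mL with impairment) = 0.5/1.5 = 0.333. The high group is 0.2 × 0.333 + 0.8 × 0.5 = 0.467 of patients. So p_high = 0.0667/0.467 = 0.143 and p_low = 0.1333/0.533 = 0.250.

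For scale, take 15,000 patients (the SAP v2.0 estimate of patients with Day 7 data), 10% mortality without impairment (assumed) and a two-sided 5% test (assumed). The chance of a falsely significant result in the protective direction is then about 3%, 18% and 97% in the three cases. With no bias it would be 2.5%.

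These are crude biases. Covariates correlated with cardiac disease, if adjusted for, would absorb part of them.

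**2. The opposing path**

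Suppose a sicker 30% of patients have odds ratio 1.25 to 2.0 for >225 mL and mortality ratio 1.5 to 2.0. The same formula gives:
- weakest: p_high 0.323, p_low 0.276, RR = 1.1613/1.1379 = 1.02
- strongest: p_high 0.364, p_low 0.222, RR = 1.3636/1.2222 = 1.12

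The acute severity items on the Risk Modifiers list could control part of this path.

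**3. Same-day deaths**

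Inputs: equal groups by intended volume, 7-day mortality 10% in each, and a fraction *d* of each group dying on Day 0, from 0.2% to 0.5%. In the extreme case, every Day-0 death in the intended high group is counted as low volume. Deaths and denominators both move:

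Apparent RR = [(0.10 − d)/(1 − d)] / [(0.10 + d)/(1 + d)]

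- d = 0.002: (0.098/0.998)/(0.102/1.002) = 0.09820/0.10180 = 0.965
- d = 0.005: (0.095/0.995)/(0.105/1.005) = 0.09548/0.10448 = 0.914

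With a landmark at the end of Day 0, both groups have mortality (0.10 − d)/(1 − d) among those still alive, so the ratio returns to 1.00. At 30 days any higher cumulative mortality would dilute this bias.

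**The case against.** **The list is not the adjustment set.** A reader might infer that SAP v5.0 excludes comorbidity from the primary model. The documents do not show this: Risk Modifiers serves future secondary strata and the primary covariates are not enumerated. This objection stands. The gap is that comorbidity is unnamed, not that it is shown to be left out. Weight, the other stated driver of volume, is on the list.

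**The protocol does not order less plasma.** A reader might take section 4.3 as an instruction to give cardiac patients less. It is a permissive example, and a slower transfusion of the same volume also satisfies it. This stands and is why the weak end of the range, close to 1, must be shown.

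**The direction is not certain.** A reader might conclude that larger volume is bound to look protective. Section 4.3 also allows larger volumes and re-treatment when the physician finds them justified, which may draw sicker patients into the upper group. This stands for the net effect.

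**The Day-0 figure is a worst case.** Section 6.1.2 gives about 200 to 250 mL per conventionally collected unit and about 200 mL or more by apheresis. One unit can therefore exceed 225 mL, and not every Day-0 death would land in the low group. This stands, so the figure is a bound.

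**Analyses are labelled exploratory and confounding is acknowledged.** Both are true, and unadjusted and adjusted results are promised. But SAP v5.0 states a primary hypothesis conditional on adjustment and points to a significance test. An acknowledgement does not supply the missing covariate, and no adjustment for baseline factors repairs the Day-0 classification.

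**Conclusion.** The point holds in limited form. The protocol makes comorbidity a determinant of the exposure, while SAP v5.0 names no pre-existing condition in a primary analysis that relies on adjustment. The volume estimate is open to confounding by comorbidity, toward apparent protection through the cardiac path if cardiac impairment raises mortality. That path alone gives about 0.84 to 0.995, and its size rests wholly on assumed prevalence, association and mortality ratio. With the opposing path at about 1.02 to 1.12, the documents do not fix the net direction.

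The same-day death rule is a separate fault in a stated rule. It pushes only toward apparent protection, by at most the step from 1.00 to about 0.965 or 0.914 at 7 days under the assumed inputs.

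That SAP v2.0 listed comorbidities is not itself a fault of v5.0. It suggests that the repair is feasible. The change should be made, with medium confidence in how much it will move the estimate.

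**What to change.** 1. State the covariates of the primary volume Cox model. Include the pre-existing conditions of the SAP v2.0 list: at least cardiovascular conditions, and also lung disease, diabetes and immunosuppressive therapy. Report the volume estimate with and without them.
2. Start the volume model at a landmark at the end of the first transfusion day. Report the number of excluded Day-0 deaths by volume group.
3. Add remdesivir and steroids only if start dates show use before transfusion. SAP v2.0 lists them as medications during hospitalization, without start dates, so they may be post-transfusion variables.

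**Cost.** This is SAP wording and a refit with items that SAP v2.0 already listed. A rule for missing comorbidity data is needed. Day-0 deaths leave the volume model only, so its estimate applies to patients who survive the first day. The landmark does not deal with transfusions stopped early in patients who survive Day 0; these stay in the low-volume group, and the report should say so. None of this changes how plasma is given.

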## Primary Analysis Plan

### Preparation of the survival endpoint: The timing of death is recorded only with the precision of a calendar day, so adjustments are needed to develop the survival estimates. For deaths that occur on the same day of transfusion, a death indicator representing 0.5 days will be administratively assigned. Otherwise, the number of days between the date of the first transfusion and death will be calculated for each participant. For patients transfused without a death record recorded as an SAE, or more precisely, on the death case report form, they are assumed to be alive. Within the context of the report and programming, this is denoted as the "immortal" survival assumption. To minimize extrapolation of the survival curves beyond a reasonable time that this assumption could be upheld, survival estimates are limited to 30 days; however, the report does introduce stopping the survival curves early, for example, at Day 7 for 7-Day mortality estimates.

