6.1.2 DOSING AND ADMINISTRATION

For practical purposes in the current outbreak, one – two units of COVID-19 convalescent plasma will be

administered. This will be provided by a registered or licensed blood collector and will be collected preferably by apheresis (total volume of plasma to be administered will be approximately 200 mL or more), or if necessary, by conventional methods (volume of plasma to administer approximately 200- 250 mL per unit). Individual institutional guidelines for the administration of plasma should be followed, including the use of any premedications, such as acetaminophen and diphenhydramine.

**If a subsequent unit of convalescent plasma is transfused**, the treating physician will begin the transfusion at a time that is clinically compatible with the patient’s underlying condition.

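### First-day plasma volume is still accruing while same-day deaths already count as events, which biases the volume contrast towards higher volume by an unknown amount

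*Supplement*

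**What the plan says.** The primary hypothesis in SAP v5.0 (Statistical Hypotheses) names volume as one of three exposures expected to affect 7-day and 30-day mortality, and defines it as "the volume of plasma initially given (i.e., on the first transfusion day". Primary Data Analysis repeats that window and says that "for the primary analysis, a spilt at 225 ml was implemented". It gives the meaning of the cut: "This effectively separates people that received 1 unit (~ 200ml) from those that deliberately received more than 1 unit of plasma".

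Under Preparation of the survival endpoint, "The timing of death is recorded only with the precision of a calendar day". For deaths after the transfusion day, "the number of days between the date of the first transfusion and death will be calculated for each participant". Deaths on the day itself stay in as events: "For deaths that occur on the same day of transfusion, a death indicator representing 0.5 days will be administratively assigned".

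Protocol v10.0, section 6.1.2, sets no interval between units. If a further unit is given, "the treating physician will begin the transfusion at a time that is clinically compatible" with the patient's condition. The same section puts a conventional unit at about 200 to 250 mL and apheresis plasma at about 200 mL or more.

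SAP v5.0 describes no landmark, no exclusion of same-day deaths from the volume contrast, no time-dependent volume term and no sensitivity analysis on this point.

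**The concern.** An exposure used as a baseline covariate should be settled when follow-up starts. Here the first transfusion day is both the window in which volume accumulates and the first day at risk. To be counted as having had more than one unit, a patient generally has to live long enough to receive the second. Someone meant for two units who dies after the first is analysed as a one-unit patient, and the death is charged to the low-volume group.

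The error runs one way: it takes deaths out of the high-volume group and adds them to the low-volume group. It enters crude mortality, the Cox hazard ratio and the bootstrap relative risk alike. Adjusting for age, severity or ICU status does not help, because it is the outcome itself that cuts the exposure short. In a non-randomised programme, a volume gradient may be read as evidence that plasma works, so a built-in tilt towards more plasma matters.

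**Working it through.** The plan states no figure to reproduce: there is no same-day death count, volume distribution, event rate or power statement for this analysis. The check has two parts.

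**Structure (from SAP v5.0 and protocol v10.0)**

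| Element | Rule |
|---|---|
| Start of follow-up | date of first transfusion |
| Exposure window | that same date |
| Deaths on that date | kept, time set to 0.5 days |
| Death time precision | calendar day |
| Second unit | after the first, at the physician's discretion |

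Exposure window and risk time overlap for one calendar day. Units given on later days do not enter the volume variable, so the bias is confined to same-day deaths.

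**Size (all inputs assumed; no true volume effect)**

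- f = share intended for more than 225 mL on day 0
- q = risk of death on day 0
- s = share of those deaths that occur before the second unit
- u = share whose first unit alone exceeds 225 mL
- m = mortality by the horizon (10% at 7 days, 25% at 30 days)

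Share of all patients moved from high to low: x = f·q·s·(1−u).
RR (high vs low) = [(f·m − x)/(f − x)] ÷ [((1−f)·m + x)/(1 − f + x)].

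Example: f = 0.4, q = 1%, s = 0.5, u = 0 gives x = 0.002. At 7 days, RR = (0.038/0.398) ÷ (0.062/0.602) = 0.0955/0.1030 = 0.927. At 30 days, RR = (0.098/0.398) ÷ (0.152/0.602) = 0.975.

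With f = 0.4 and u = 0:

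| q | s | 7-day RR | 30-day RR |
|---|---|---|---|
| 0.5% | 0.1 | 0.993 | 0.998 |
| 0.5% | 0.5 | 0.963 | 0.988 |
| 1% | 0.5 | 0.927 | 0.975 |
| 2% | 0.5 | 0.858 | 0.951 |

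If 30% of first units alone exceed 225 mL (u = 0.3), the 0.927 becomes 0.949 and the 0.993 becomes 0.995.

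**Check with Cox fits.** Null data were simulated with N = 15,000, f = 0.5, s = 0.5, u = 0.3, 7-day mortality 10%, and 60 replicates per setting. N is only a scale, borrowed from SAP v2.0's estimate of patients with Day 7 data.

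| q | HR as written (null rejected) | HR from end of day 0 (null rejected) |
|---|---|---|
| 0.25% | 0.977 (5%) | 0.995 (3%) |
| 0.5% | 0.958 (7%) | 0.991 (5%) |
| 1% | 0.937 (28%) | 1.006 (7%) |

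Sixty replicates give rough rejection rates: the standard error at 5% is √(0.05·0.95/60), about 2.8 points. A normal approximation with the same inputs gives a 9% chance at q = 0.5%, and 25% at q = 1%, of a significant result favouring high volume, against 2.5% nominal in that direction.

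**The case against.** The strongest reply is that the bias may be trivial. Every input to its size is assumed, and the most influential, the share of same-day deaths that precede the second unit, depends on how quickly units follow one another. Section 6.1.2 allows units back to back, which would make that share small. At 0.5% same-day deaths or fewer, the simulated rejection rates are close to nominal. This stands: the direction is established, the size is not.

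Three stronger readings are tempting, and the documents do not support them.

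- A reader might infer that every patient who dies before a second unit is forced into the low group. The cut is in mL, not units, and section 6.1.2 allows a single unit above 225 mL. Such patients are classed high, which weakens the bias without reversing it.
- A reader might blame the 0.5-day value. It only gives a positive time to deaths dated to the day; any other time within day 0 leaves the bias in place. The cause is the overlap of exposure window and follow-up.
- A reader might extend the point to the antibody exposure, since the hypothesis speaks of a quantity of antibodies. Primary Data Analysis works with titer levels and a low/high split. A titer does not automatically rise with a second unit, and the SAP does not say how titers are combined across units, so no direction of bias follows.

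The remedy also has a price. Starting at the end of day 0 discards any same-day harm that volume might cause, and protocol section 4.3 itself notes that patients with cardiac impairment may need less volume. This supports keeping the as-written analysis in view. It does not support leaving that analysis to stand alone. Finally, protocol v10.0 calls all analyses exploratory (section 9.1), which lowers the stakes but does not remove a bias of known direction.

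**Conclusion.** The concern holds for the volume contrast. SAP v5.0 lets exposure form during time at risk, so same-day deaths before an intended second unit generally fall in the group at or below 225 mL, and higher volume is spuriously favoured.

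Under no true effect and the assumed inputs (40% intended for higher volume, 10% mortality at 7 days), the 7-day relative risk lies between about 0.99 and 0.86. These are illustrations, not bounds: if all same-day deaths preceded the second unit, 1% such deaths would alone give 0.858. At 30 days, with 25% mortality, the same scenarios give about 0.998 to 0.951. The actual number of same-day deaths by units received would largely settle the matter. Nothing here shows that any volume effect found would be an artefact.

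This is a separate matter from what the SAP calls its immortal survival assumption, which treats patients without a death record as alive.

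**What to change.** For the volume contrast only:

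1. Start follow-up at the end of the first transfusion day (landmark Day 1), when first-day volume is fixed. Keep Day 7 and Day 30 counted from the date of first transfusion.
2. Tabulate same-day deaths by volume group and by number of units received.
3. Show the as-written analysis next to the landmark analysis.
4. Keep same-day deaths, with the 0.5-day rule, in overall mortality. No change to the titer analysis follows from this point.

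The landmark needs only the calendar dates that the SAP already uses. A time-dependent volume term would need clock times for both death and transfusion, and death is recorded only to the day.

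Cost: one changed start time in the volume models and one table. The landmark estimate applies to patients who survive day 0 and would miss any same-day harm of volume; the table and the as-written analysis keep that visible.

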**8 STUDY ASSESSMENTS AND PROCEDURES**

8.1 EFFICACY ASSESSMENTS

Patient demographic information will be obtained to include age and sex

Assessments for potential efficacy are exploratory as part of this expanded access program but may include web-based collection of the following information:

1. Acute care facility length of stay
2. Number of days in an intensive care unit
3. Number of days on mechanical ventilation
4. Survival until discharge from an acute care facility

An exploratory analysis may be conducted correlating the level of neutralizing antibody titers with clinical outcomes observed.

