8.2 SAFETY AND OTHER ASSESSMENTS

Reporting is required for serious adverse events (SAEs); and we will ask the treating physician when reporting the event to determine if the event is potentially related to the administration of the COVID- 19 convalescent plasma.

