8.3 ADVERSE EVENTS AND SERIOUS ADVERSE EVENTS

Serious adverse events should be reported, by the treating physician to the sponsor/principal investigator using the forms provided on the website ([www.uscovidplasma.org](http://www.uscovidplasma.org/)).

The sponsor/principal investigator is responsible for filing reports to the FDA and IRB as required.

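### The SAP v5.0 death rule is unclear about a fatal SAE without a death form, leaves out other planned vital-status records, and has no reconciliation step, so a death recorded only there is scored as survival to Day 30

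*Supplement*

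**What the plan says.** SAP v5.0, Statistical Hypotheses, makes mortality the primary outcome: "7-Day and 30-Day mortality will be affected by plasma transfusion dynamics after adjustment for pre-disposing risk factors". The paragraph on preparing the survival endpoint sets the event rule. Transfused patients "without a death record recorded as an SAE, or more precisely, on the death case report form, they are assumed to be alive". The SAP calls this the immortal survival assumption and limits its reach: "survival estimates are limited to 30 days", with curves also stopped at Day 7.

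Protocol v10.0 plans vital-status information by more than one route.

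- **SAE reports.** Section 8.3: "Serious adverse events should be reported, by the treating physician to the sponsor/principal investigator using the forms provided on the website".
- **Survival to discharge.** Section 3 lists it as a tertiary/exploratory endpoint. The synopsis says it will be collected retrospectively. Section 8.1 lists "Survival until discharge from an acute care facility" among items that may be collected.

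SAP v2.0 is superseded, but it shows what the database was expected to hold: it drew known vital status from a daily summary and a Day 7 follow-up assessment. Neither SAP v5.0 nor protocol v10.0 says how these records are compared with each other or with the death form.

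**The concern.** The SAP rule is affirmative. It does not leave status unknown when the death record is absent; it assigns survival up to Day 30. That makes the list of sources that count as a death record decisive, and the list is both ambiguous and short.

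It is ambiguous because the sentence first accepts a death recorded as an SAE and then narrows this to one form. A programmer cannot tell whether a fatal SAE report without that form is an event. It is short because discharge status and follow-up assessments are not named.

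The error can run in one direction only, turning deaths into survivors. It would enter the crude rates, the Cox models and the adjusted survival curves alike. This differs from missing follow-up, where nobody has recorded the patient's status. Here a death has been recorded and the rule does not read the record, so censoring at the last date known alive would not by itself repair it.

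**Working it through.** **Step 1: apply the rule literally.** Take three patients who die within 30 days of first transfusion.

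| Where the death is recorded | Status under SAP v5.0 |
|---|---|
| Death case report form | Event |
| SAE report with fatal outcome, no death form | Unclear: event on the first half of the sentence, alive on the second |
| Discharge or follow-up status only | Alive to Day 30 |

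The third row follows because the rule does not name those fields and no reconciliation step is described. The documents give no figure on this point to reproduce, so the rest is illustration.

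**Step 2: inputs.** The share *d* of deaths lacking a counted record is not in the documents; 1% to 10% is assumed. True mortality *m* is assumed to be 25%, with 15% and 30% as alternatives. For scale only, the group size is half of the roughly 15,000 transfusions that SAP v2.0 expected to have Day 7 data, treated as patients: 15,000 / 2 = 7,500 per group.

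**Step 3: absolute mortality.** Scored mortality = *m*(1 − *d*), so the loss is *m* × *d*. At *m* = 25%:

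- *d* = 1%: 0.25 percentage points
- *d* = 5%: 1.25 points
- *d* = 10%: 2.5 points

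**Step 4: risk ratio.** Scored RR = true RR × (1 − *d*₁)/(1 − *d*₂). Equal losses cancel. With a true RR of 1 and losses of 5% and 10%, the scored RR is 0.95/0.90 = 1.06, or 0.90/0.95 = 0.95 the other way round.

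**Step 5: the same shift against sampling error, with all the loss in one group.** SE(log RR) = √[2(1 − *m*)/(*m* × 7,500)]. At *m* = 25% this is √[1.5/1,875] = 0.0283. The shift is |ln(1 − *d*)|:

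| *d* in one group | Shift in log RR | In SE |
|---|---|---|
| 1% | 0.0101 | 0.36 |
| 3% | 0.0305 | 1.1 |
| 5% | 0.0513 | 1.8 |
| 10% | 0.1054 | 3.7 |

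Over 1% to 10%, the range is 0.26 to 2.7 SE at *m* = 15% (SE 0.0389) and 0.40 to 4.2 SE at *m* = 30% (SE 0.0249).

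**The case against.** The strongest reply is that there is probably one route, not several. Section 8.3 has SAEs filed on the programme's website forms, so the death form may simply be the SAE report for a fatal event, and the SAP's second clause only names it. That is a natural reading. If it is right, the second row of the table in Step 1 collapses into the first, and one clarifying sentence settles it. The third row remains.

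A reader might infer three stronger things that the documents do not support.

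- **That protocol and SAP define death differently.** The protocol does not define death. It lists SAEs and survival to discharge as endpoints or data items.
- **That the SAP ignores SAE reports.** Its rule names a death recorded as an SAE.
- **That any gap between survival to discharge and 30-day mortality would come purely from the choice of source.** The horizons differ. The SAP counts from first transfusion. Under section 4.5 participation runs to discharge or to 30 days after the most recent transfusion, whichever is first, and section 4.3 allows repeat transfusions. An in-hospital death after Day 30 from first transfusion can count under one and not the other with identical sources.

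It is also fair to say that the case report forms are not in the supplement, that section 8.1 makes discharge survival optional while the synopsis does not, and that no passage shows discordant records or form completion varying by exposure. Sections 9.1 and 9.4 declare the analyses exploratory, and the SAP states its assumption openly. These points limit the size of the concern. They do not supply the missing source list.

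**Conclusion.** The point holds as a gap in the event definition for the primary outcome. The rule is unclear about a fatal SAE without the death form, omits planned vital-status records, and has no reconciliation step. A death recorded only in those other places would be scored as survival to Day 30.

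That such deaths occurred is not shown; their number is unknown and may be small. The direction for absolute mortality is certain: downward, by *m* × *d*. The effect on the risk ratio is conditional. It is nil if the loss is equal across exposure groups and reaches the Step 5 figures only if the whole loss falls in one group. Those figures rest entirely on assumed shares, an assumed mortality and a group size taken for scale from a superseded plan. Form completion could vary with hospital or calendar period, but the documents do not say that it did. Of these two, calendar month is on the SAP's list of risk modifiers and hospital is not.

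The change should be made because it corrects a one-directional error in the primary outcome at little cost.

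**What to change.** In SAP v5.0, under preparation of the survival endpoint:

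1. Count as a death any death recorded on the death form, as an SAE with fatal outcome, or as a discharge or follow-up status of died, wherever those fields are collected.
2. State which date is used when sources disagree, and what is done when the date is missing.
3. Query discordant records before data lock.
4. Tabulate deaths by source and by exposure group, so that readers can see how many depend on each source and whether this differs between groups.

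The cost is SAP wording, one extra merge and some site queries. Reported mortality may rise slightly. Treatment of patients whose status is not recorded anywhere is a separate matter and needs its own rule.
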